### Assessments and outcomes

Assessors masked to treatment group will collect outcome variables at baseline, 17-weeks, 27-weeks (after therapy cessation/TAU), and 52-weeks (see Fig. 2 for schedule of enrolment, intervention and assessments). Assessments will be via semi-structured interviews and self-report questionnaires. Participants will be compensated for the time taken at each data collection point (£20). Contact will be made at 39-weeks to promote retention and re-confirm contact details. Participants will have flexibility to choose when and where they would like to be seen e.g. in non-stigmatising settings such as their home, youth centres, colleges, or primary care centres. Measures to be collected are listed below.

**Fig. 2 Fig2:**
[figure not shown]
Schedule of enrolment, intervention and assessments

#### Demographic information

Demographic information will be collected at baseline including sex, gender, age, sexual orientation, and ethnicity. An additional demographics form capturing education, employment, marital status, living arrangements, receipt of benefits and criminal convictions will be completed at baseline and then checked at the 27- and 52-week follow-ups for changes.

#### Co-primary mood outcome measure

The SCID-5-RV with Psychiatric Status Ratings (PSR), which incorporates the SCID Longitudinal Follow-Up Evaluation (LIFE) [50], is used to assess the severity of depressive and manic symptoms over the prior 4 weeks, with measurements taken at the 27-week timepoint. Two scores are provided, depression (on which the sample size is primarily based), and mania.

#### Secondary outcomes

Appraisals of and responses to mood (hypothesised mechanisms).

The following self-report measures will assess key components of the predicted psychological pathways to mood swings:Hypomanic Positive Predictions Inventory (HAPPI) [51] assesses multiple, extreme, and personalised appraisals about high and low mood.Behaviours Checklist (BC) [52] measures ascent and descent behaviours triggered by extreme positive and negative appraisals about internal states.Internal States Scale (ISS) [53] assesses internal mood states and has four subscales: Activation, Depression, Well-Being, and Conflict.

### Secondary mood outcome measures

Beck Depression Inventory 2nd Edition (BDI-II) [54] assesses severity of depression.Altman Self-Rating Mania Scale (ASRM) [55] assesses the self-reported presence of and/or severity of mania symptoms.Young Mania Rating Scale (YMRS) [56] assesses severity of mania.

### Additional Secondary Outcome Measures

The Global Assessment of Functioning scale (GAF) [57] measures social, occupational, and psychological functioning.Social and Occupational Functioning Assessment Scale (SOFAS) [58] is a global rating of current functioning.World Health Organisation Quality of Life (WHOQOL-BREF) [59] will be administered to assess quality of life.Metacognitions Questionnaire–30 (MCQ-30) [60] is a self-report measure that assesses metacognitive beliefs related to worry and intrusive thoughts.Desire Thinking Questionnaire (DTQ) [61] measures metacognitions about desire thinking, which is the verbal and imaginal elaboration of a desired target.Brief Core Schema Scale (BCSS) [62] measures core beliefs about the self and others and has four subscales (negative-self, positive-self, negative-other, and positive-other).Response Style Questionnaire (RSQ) [63] is a self-report measure of stable trail-like behaviours observed in response to depression.Pittsburgh Sleep Quality Index (PSQI) [64] assesses sleep quality.Positive and Negative Sleep Appraisal Measure (PANSAM) [65] assesses for extreme positive and negative sleep appraisals with regards to sleeping more or less than usual.

### Health economics measures

Measures collected to inform health economic analysis include:EQ-5D-5L [66] measure of health status is a generic measure for describing and valuing health on 5 domains: Mobility, Self-Care, Usual Activities, Pain/Discomfort, and Anxiety/Depression, and overall health.Recovering Quality of Life (ReQoL-10) [67] measures domains that are relevant to the recovery of people with mental health difficulties.Service use questionnaire adapted from previous trials, collecting data on inpatient, outpatient, accident and emergency, primary, community and social care use.

### Therapy session measures

For those in the intervention arm, a 10-item HAPPI is derived from the full measure [51], incorporating a mixture of positive and negative beliefs given the evidence that the co-occurrence of these beliefs is highly predictive of mood swings [35]. This 10-item self-report measure is completed at each session alongside the ISS [53] and the Beck Depression Inventory – Fast Screen (BDI-FS) [68]. The measures are used to guide interventions and track change over time.

### Measures of alliance, engagement, and adherence

All participants will complete, a Facilitative Alliance Inventory (FAI) [69] at baseline, 27-week and 52-week follow-ups to assess alliance with the researchers. For those in the intervention arm, therapeutic alliance will be assessed after session 4 and 10 with the California Psychotherapy Alliance Scale (CALPAS) [70] completed by both the therapist and participant. Therapists will record the number of sessions attended, duration of the sessions, and the session record form as a measure of adherence.

### Nested qualitative study

The qualitative component explores perceived mechanisms of change through individual semi-structured interviews with a maximum variance sample of participants selected for their varying therapeutic alliance scores, post-intervention mood experiences, and appraisal changes. We will also examine CBT_BAR_ implementation in NHS services through individual semi-structured interviews with key stakeholders (e.g., family members, healthcare professionals, and service providers) across multiple sites.

### Data management

Study data are collected using paper Case Report Forms and transferred to a secure, web-based software platform (REDCap) [71, 72] hosted by York Trials Unit, who provide data management and oversight. Access to the study interface will be restricted to named authorised individuals granted user rights by a REDCap administrator at York CTU. All data will be kept secure at all times and maintained in accordance with the requirements of GDPR and archived according to GCP regulations.

### Sample size and power calculations

This trial has two co-primary outcomes (4-week average Longitudinal Follow-Up Evaluation (LIFE) [50] depression and mania PSR (Psychiatric Status Ratings). However, the overall symptom severity of LIFE [50] depression is greater than that of mania in this population, as is its standard deviation (SD), and therefore a larger sample size is required for the depression component compared with the mania component [73]. Therefore, sample size is based primarily upon parameters from the depression component. Although the minimally clinically important difference (MCID) in LIFE [50] PSR mania score is somewhat smaller than the MCID for the LIFE [50] depression score, the relative difference will be smaller than that for the SD. Overall, the standardised effect size will be smaller for depression than mania, thus leading to a larger sample size. On the LIFE [50] PSR, our eligible population will score at the higher end of the subthreshold range (3–4) as those scoring 5–6 will confer research diagnostic criteria and therefore not meet the inclusion criteria for the trial. Based on our feasibility trial [74] where participants had a mean baseline BDI-II score of 37.9, participants will tend to be towards the upper end of the subthreshold range. We therefore expect our LIFE [50] depression PSR score to be 3.75. Button [75] reported that a MCID for the BDI-II is around 17–18%. Given that we expected similar sensitivity for the mean LIFE depression PSR scores as would be the case for BDI-II, a difference of around 0.5 points (0.18*[3.75–1] = 0.50 to 2 decimal places) on the PSR for LIFE [50] depression will be considered the minimum in order to indicate that CBT_BAR_ is having an important effect.

Assuming a SD of 1.3 [73], a conservative correlation of 0.4 between baseline and 27-weeks [76] a 2.5% two-sided significance level, and a between group mean difference of 0.5 points in mean 4-week PSR for LIFE [50] depression at 27-weeks, we would require 286 participants with outcome data to achieve 90% power. Inflating the sample size to allow for a conservative 15% attrition (13% in the feasibility trial) [74] requires a target to randomise of 338 participants (approximately 68 per site). This sample size would also provide 98.5% power to detect a more conservative MCID on LIFE [50] PSR for mania, target effect of 0.25 points, estimated within-group SD = 0.5 points [73]. In each case, power will be increased due to the (multiple) correlation between outcome and the full set of explanatory variables adjusted for in the model. A random therapist effect is not accounted for in our sample size calculation as the effect on the BDI-II in our feasibility trial was 0, although the confidence interval was wide. This will be explored within a sensitivity analyses.

For the qualitative component we will recruit two groups of 15–25 people each for individual interviews. One group will be participants from the intervention arm of the trial across all five sites and one group will comprise key stakeholders including health professionals, service providers and commissioners. To build upon the acceptability work in the original BART trial, we will seek a more diverse and inclusive sample (e.g. ethnicity, socioeconomic status, gender) and level of engagement in therapy, including non-responders. The stakeholder groups will include health professionals involved in delivery of CBT_BAR_ and other interventions and services for this population, and referrers (and potential referrers) to the trial from a range of services and across geographical area.

#### Data analyses

Quantitative analyses will be undertaken using the principles of intention-to-treat, where participants are analysed according to the group to which they were randomised, regardless of what treatment they received. Analysis will be undertaken using Stata v18.0 (or later) [45], using two-sides tests at a 2.5% significance level, with 97.5% confidence intervals provided, unless otherwise stated. All quantitative analyses will be pre-planned and included in a Statistical Analysis Plan which will be finalised and approved by the TSC prior to database lock and analysis.

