#### Secondary outcomes

Secondary outcome measures (including the primary outcome measures at the other follow-up time-points) will be analysed using generalised linear models, with link function appropriate to the type of data. Models will be adjusted in the same way as the primary outcome, using the baseline value of the outcome measure (where applicable). Time to events (transition to first episode (hypo)mania and recovery from BAR symptoms) will be analysed using a Cox proportional hazards model, adjusted for stratification factors. Tests will use a 5% significance level and two-sided 95% CIs will be presented.

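### A cheap improvement, not an error: Holm's step-down in place of a fixed 2.5% per co-primary outcome would raise depression power from about 90% to about 94% if mania responds as planned

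*Protocol article*

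**What the plan says.** The Sample size and power calculations section opens with "This trial has two co-primary outcomes", the four-week mean LIFE ratings for depression and for mania. It sizes the trial on depression at "a 2.5% two-sided significance level", giving 286 participants with outcome data for 90% power and 338 to randomise. For mania it adds: "This sample size would also provide 98.5% power to detect a more conservative MCID on LIFE [50] PSR for mania".

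The Data analyses section sets the general rule: "using two-sides tests at a 2.5% significance level, with 97.5% confidence intervals provided, unless otherwise stated". The Co-primary outcomes section gives no other level. The only departure is for secondary outcomes: "Tests will use a 5% significance level and two-sided 95% CIs will be presented".

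Design and analysis therefore agree on a fixed two-sided 2.5% per co-primary outcome. The 5% family total is implied (2 × 2.5%) rather than stated. The article does not say whether one successful outcome is enough, and it gives no step-down rule. It refers to a statistical analysis plan, to be finalised before database lock, which is not available here.

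**The concern.** Testing each of two outcomes at 2.5% protects a claim based on either one. Once one outcome has passed at 2.5%, the other can be tested at 5% without raising the family error above 5%. The fixed rule does not use this.

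The loss falls mainly on depression, the outcome that sets the sample size. By the plan's own figures mania is very likely to pass, so depression would usually qualify for the 5% level. As written, a depression p-value between 0.025 and 0.05 is negative even when mania has already succeeded.

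**Working it through.** **Inputs**, all from the Sample size and power calculations section.
- Depression: "Assuming a SD of 1.3"; "a conservative correlation of 0.4 between baseline and 27-weeks"; "a between group mean difference of 0.5 points in mean 4-week PSR".
- Mania: difference 0.25, SD 0.5.
- Two-sided level 2.5%; 286 completers.
- Assumed: 1:1 allocation (143 per arm), since the ratio is not stated but 1:1 reproduces the plan's sample size.
- Assumed: the correlation between the two test statistics, which is not given. It is varied from −0.3 to 0.7.

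**Step 1. Reproduce the plan.**
- Baseline-adjusted SD = 1.3 × √(1 − 0.4²) = 1.1915.
- n per arm = 2 × 1.1915² × (2.241 + 1.282)² / 0.5² ≈ 141, or 282 in total, against 286 stated.
- 286 / 0.85 = 336.5, so 337, against 338 stated.
- Standard error of the depression difference at 143 per arm = 1.1915 × √(2/143) = 0.1409. Expected z = 0.5 / 0.1409 = 3.548.
- Power at 2.5% = Φ(3.548 − 2.241) = 90.4% (90.2% by noncentral t), against 90% stated.
- Mania: standard error = 0.5 × √(2/143) = 0.0591; expected z = 4.228; power at 2.5% = Φ(4.228 − 2.241) = 97.7%. With a baseline correlation of 0.4 it is 99.1%. The stated 98.5% lies between.

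The plan's figures reproduce. The steps below use the lower mania figure.

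**Step 2. Depression power under Holm.**
- Depression power at 5% = Φ(3.548 − 1.960) = 94.4%. This is the ceiling.
- Holm power = P(p_dep < 0.025) + P(0.025 ≤ p_dep < 0.05 and p_mania < 0.025).
- With independent tests: 0.9044 + (0.9439 − 0.9044) × 0.9765 = 0.943.
- By simulation (1,000,000 draws per setting), correlations −0.3 to 0.7: 94.0% to 94.4%.

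**Step 3. Power for both outcomes.**
- Fixed rule, independent tests: 0.9044 × 0.9765 = 88.3%.
- Holm needs both below 0.05 and at least one below 0.025. With mania power at 5% of 98.8%: 0.9439 × 0.9883 − 0.0395 × 0.0118 = 93.2%.
- Simulated, correlations 0 to 0.5: 88.3–89.1% (fixed) against 93.2–93.5% (Holm).

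**Step 4. Dependence on the mania effect** (SD 0.5; depression effect as planned).

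| True mania effect | Mania power at 2.5% | Depression, fixed rule | Depression, Holm, correlation 0 to 0.5 | Depression, Holm, correlation −0.3 to 0.7 |
|---|---|---|---|---|
| 0.25 | 97.7% | 90.4% | 94.1–94.3% | 94.0–94.4% |
| 0.20 | 87.3% | 90.4% | 93.2–93.9% | 92.7–94.2% |
| 0.125 | 44.9% | 90.4% | 91.1–92.2% | 90.7–92.9% |
| 0 | 2.5% | 90.4% | 90.6% | 90.5–90.6% |

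**Step 5. Family error.** Simulated under no effect on either outcome, and under an effect on only one, with correlations 0, 0.3 and 0.7, Holm's family error was at most 4.9%.

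**Step 6. Intervals.** A 97.5% interval extends 2.241 standard errors either side of the estimate. A p-value above 0.025 means the estimate is less than 2.241 standard errors from zero, so the interval includes zero. Every result that Holm adds has p between 0.025 and 0.05, so every one has this mismatch.

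**The case against.** The strongest reply is that nothing here is wrong. The fixed 2.5% is pre-specified, controls the family error, is used consistently in design and analysis, and already gives 90% power. That stands. A reader might infer from the label co-primary, or from the lost power, that the testing rule is mistaken. The document does not support this. A rule requiring both outcomes to succeed would need no split, so the 2.5% level points to an either-outcome claim, for which the split is legitimate.

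It would also be too strong to call the change free. Under the present rule each test agrees with its 97.5% interval; under Holm some will not. Matching intervals are a respectable reason to stay with the single-step rule.

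The 94% is conditional on mania, and the gain is about 4 points at most. The article also expects the full covariate set to raise power further. If the multiple correlation were 0.5 (an assumption), depression power would be about 93.5% at 2.5% and 96.4% at 5%, so the most that could be gained is about 3 points.

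Finally, the unseen analysis plan may already contain a step-down rule. The article does not show one, and it does not defer the level: it states 2.5% and derives the sample size from it.

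**Conclusion.** The point holds as an optional efficiency gain. At the plan's own effects and 286 completers, Holm lifts depression power by about 4 percentage points (90% to 94%), which cuts the chance of missing a true 0.5-point difference from about 10% to about 6%. Power for both outcomes rises by about 4 to 5 points. Sample size and the 5% family limit are unchanged, and power on neither outcome can fall.

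This rests on three assumptions: a claim on either outcome is intended, allocation is 1:1, and mania responds by roughly the planned 0.25 points. If mania does not respond, the gain all but disappears.

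**What to change.** Before database lock, and before any comparison by arm is seen, add to the analysis plan:
- Efficacy is claimed if either co-primary outcome is significant.
- The two p-values are tested by Holm: the smaller against 0.025 and, if that is significant, the larger against 0.05.
- Holm decides significance. The 97.5% confidence intervals are simultaneous intervals and may include zero for an outcome that Holm declares significant.

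If the intention is instead that both outcomes must succeed, say so; the 2.5% split is then unnecessary and Holm is not the remedy.

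The cost is a few sentences and the possible mismatch between test and interval. No extra participants are needed.

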#### Co-primary outcomes

The primary analyses for each of the co-primary outcomes (mean 4-week PSR for LIFE depression score and for LIFE mania score at 27-week follow-up) will use analysis of covariance, with adjustment for the stratification factors (site and BAR group), the baseline PSRs for depression and mania and prior CBT (yes/no). For each outcome, if less than 15% of participants are excluded from the analysis due to missing data, and the differential amount of missing data between the trial arms is less than 10% then complete case analysis will be used. Otherwise, multiple imputation by chained equations (MICE) [77] will be used, assuming that the data are ‘missing at random’. The opposite method will be used as sensitivity analysis. To explore whether BAR group and prior CBT could act as potential moderators of the co-primary outcomes, the analysis will be repeated with the inclusion of interaction term, for each of these variables with treatment arm, separately.

Casual inference methods for mediation [78] will be used to estimate the indirect effect of CBT_BAR_ on each of LIFE mania and LIFE depression scores via the HAPPI total score at the preceding time-point (e.g. 17-week HAPPI for 27-week LIFE scores). A more complex causal model incorporating Behaviours Checklist and Internal State Scale will be investigated using structural equation modelling. As a post-randomisation effect modifier, the impact of the number of CBT_BAR_ sessions attended will be assessed using principal stratification methods; other measures of intervention receipt, including antidepressant medication, will be considered in separate analyses.

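### The co-primary depression model is valid and meets its stated power, but adding baseline BDI-II, already collected, would gain a little precision at almost no cost

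*Protocol article*

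**What the plan says.** The section Co-primary outcomes fixes the covariates of both primary models: site and BAR group, as stratification factors, then "the baseline PSRs for depression and mania and prior CBT (yes/no"). No other baseline symptom score is listed.

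The section Secondary mood outcome measures includes a finer depression scale: "Beck Depression Inventory 2nd Edition (BDI-II) [54] assesses severity of depression". YMRS and ASRM are listed there for mania. According to Assessments and outcomes, masked assessors "will collect outcome variables at baseline" and at each follow-up. The Secondary outcomes analysis section adjusts each secondary model for that measure's own baseline value where applicable, so the planned BDI-II analysis already relies on a baseline BDI-II.

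Sample size and power calculations expects entrants to score in the upper subthreshold PSR range, 3–4, with a depression score of 3.75. The calculation itself rests on this: "Assuming a SD of 1.3 [73], a conservative correlation of 0.4 between baseline and 27-weeks", with "a 2.5% two-sided significance level" and a target difference of 0.5. It then adds that "power will be increased due to the (multiple) correlation between outcome and the full set of explanatory variables adjusted for in the model".

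**The concern.** A baseline covariate helps only as far as it predicts the outcome. If nearly all entrants fall within one point of each other on the baseline depression PSR, that score has little room to explain a 27-week outcome with SD 1.3. BDI-II has a wider range, is taken at the same visit, and is used by the plan to place the expected PSR level. The plan also looks to its covariate set for some extra power, yet the set holds no symptom measure other than PSR.

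What is at stake is the width of the 97.5% interval for the depression effect, which is the outcome that drives the sample size. Prespecified adjustment for a prognostic baseline score introduces no bias and also guards against chance imbalance in severity.

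**Working it through.** **Inputs from the Protocol article (Sample size and power calculations):** SD 1.3; difference δ = 0.5; baseline correlation r = 0.4, so r² = 0.16; two-sided α = 0.025; power 90%; 286 with outcome data; 15% attrition. **Assumed:** 1:1 allocation, since no ratio is given.

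**1. Reproduce the plan's figure.** Per arm, n = 2(z₀.₉₈₇₅ + z₀.₉₀)² × SD²(1 − r²)/δ² = 2(2.2414 + 1.2816)² × 1.69 × 0.84/0.25 = 140.95. That is 141 per arm, or 282 in total. The t-based version gives 143 per arm, which is the stated 286. With attrition, 286/0.85 = 336.5, so 337, or 338 for equal arms. The plan's figure holds.

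**2. Power of the planned model at 143 per arm.** SE = 1.3 × √0.84 × √(2/143) = 0.1409. Power = Φ(0.5/0.1409 − 2.2414) = 90.4% (90.2% by t).

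**3. How much BDI-II might add.** The documents give no correlation of baseline BDI-II with 27-week PSR, so this is an assumption. With two baseline scores, total R² = (r_yp² + r_yb² − 2·r_yp·r_yb·r_pb)/(1 − r_pb²), where y is the outcome, p the baseline PSR and b the baseline BDI-II. Take r_yp = 0.4.
- If BDI-II predicts the outcome as well as PSR does (r_yb = 0.4) and r_pb runs from 0.4 to 0.8, extra R² is 0.069 down to 0.018.
- If r_yb = 0.3 over the same range, extra R² is 0.001 to 0.023, and power is 90.5% to 91.3%.

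**4. Effect on precision and power**, with SE = 1.3 × √(0.84 − extra R²) × √(2/143). Equivalent extra participants = 286 × [0.84/(0.84 − extra R²) − 1].

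| Extra R² | SE | Power | Equivalent extra analysed participants |
|---|---|---|---|
| 0 | 0.1409 | 90.4% | 0 |
| 0.02 | 0.1392 | 91.2% | 7 |
| 0.05 | 0.1366 | 92.2% | 18 |
| 0.07 | 0.1349 | 92.9% | 26 |

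**5. If baseline PSR predicts less than assumed.** A score confined to 3–4 with mean 3.75 has SD at most √[(3.75 − 3)(4 − 3.75)] = 0.433. A correlation of 0.4 with an outcome of SD 1.3 then needs a slope of at least 0.4 × 1.3/0.433 = 1.20 outcome points per baseline point. At the maximum SD, a slope of 1 gives r = 0.433/1.3 = 0.33 and power 88.6%. A slope of 0.5 gives r = 0.17 and power 85.5%. Extra R² of 0.02 to 0.07 lifts these to 89.4–91.2% and 86.2–88.1%.

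**6. Costs.** Even two added covariates raise the SE by under 0.5% through lost degrees of freedom. The larger risk is exclusion under the complete-case rule. Losing 286 × extra R²/0.84 participants for want of a baseline BDI-II cancels the gain: about 7 at 0.02, 17 at 0.05 and 24 at 0.07.

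**7. Mania.** With δ = 0.25 and SD 0.5 at 143 per arm, power is 97.7% without a baseline correlation and 98.6% with r = 0.3, in line with the stated 98.5%. Starting from 97.7%, extra R² of 0.05 gives 98.2%. There is little left to gain.

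**The case against.** The strongest reply is that nothing here is broken. The model adjusts each outcome for its own baseline, for the other co-primary's baseline, for both stratification factors and for prior CBT. It reaches 90% power from "a conservative correlation of 0.4 between baseline and 27-weeks" alone, and the plan treats the full covariate set as a bonus on top. All of this stands.

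The size of the gain is also unproven. A reader might infer that the model leaves out the best available predictors, but the documents give no evidence on prognostic strength. They use BDI-II only to place the mean PSR and to scale an important difference. If the two scales track each other closely, BDI-II becomes more redundant once PSR is in the model. Larger gains need BDI-II to predict later PSR better than baseline PSR does.

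The narrow range is an expectation and cannot be read as applying to almost everyone. The exclusion list does not name a full depressive episode, and BAR group 1 does not require depression, so real scores may spread on either side of 3–4. A wider spread would make 0.4 easier to reach. The outcome is also a four-week average; if baseline is scored the same way, it is less coarse than a single rating.

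Baseline completeness is not guaranteed. The text makes BDI-II a baseline measure, but the schedule figure is not shown, and the Patient and Public Involvement section allows questionnaires to be completed outside the appointment. The imputation rule in the fix answers this.

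Finally, the covariate list is published and recruitment was due to end in July 2025, so a late change needs to be transparent. That argues for dating and explaining it, and does not rule it out while the analysis plan is still open.

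**Conclusion.** The point holds as an optional efficiency gain for the depression model. On the plan's inputs, an assumed extra R² of 0.02 to 0.07 moves power from about 90.4% to between 91% and 93%, and narrows the SE by roughly 1% to 4% (√(0.82/0.84) = 0.988; √(0.77/0.84) = 0.957). If BDI-II is the weaker predictor, the gain can be close to nil. If the baseline PSR correlation falls below 0.4, power starts below 90% and BDI-II could recover part of the shortfall.

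A reader might infer that the trial is underpowered, that the primary analysis is biased, or that both co-primary outcomes lose materially. The documents support none of these: the sample size reproduces, the ANCOVA is valid, and stated mania power is already 98.5%.

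**What to change.** Before database lock, and before anyone sees outcome data by arm, prespecify baseline BDI-II as a linear covariate in the depression ANCOVA, in its partially nested therapist version and in the longitudinal mixed-model version. Keep all covariates already listed. Fill any missing baseline BDI-II with the mean over both arms combined, so that nobody is excluded and the 15% missing-data trigger is not affected by this covariate. If the multiple imputation branch applies, include BDI-II in the imputation model. Adding baseline YMRS to the mania model on the same terms is optional.

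The cost is one degree of freedom, a few lines in the statistical analysis plan and a missing-baseline rule. No new data are needed. Because the covariate list is in the published protocol, record the change with its date and reason. If it is handled as a protocol amendment, the Trial monitoring section makes it reportable to the funder, sponsor and ethics committee.
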